### Randomization and patient allocation

Subjects will be randomly allocated into one of the three treatment arms by a 1:1:1 treatment ratio: (1) true acupuncture + metformin placebo, (2) sham acupuncture + metformin, and (3) sham acupuncture + metformin placebo. The Data Coordination Centre (DCC) statisticians will generate the randomization scheme for the study. The true and sham acupuncture treatments will be known only to the acupuncturists besides the DCC data manager. The metformin and placebo having the same package will be organized in a kit consisting of 4 sacks for each subject with 336 tablets in total, respectively. The kit will be labeled with an ID number mapped to the metformin and placebo known only to the DCC personnel. The metformin and placebo assignments will be double-blind to any site investigators.

A central randomization system will be used to allocate patients. Patients will be stratified based on three sites and randomly assigned. The *Chinese Clinical Trial Registry* takes the responsibility for generation of the random number sequence by computer software, and the allocation sequence is deposited in ResMan, a web-based database. When a new participant enrolls, the allocation information will be obtained by inputting a special password in ResMan. It is not possible to speculate the allocation status of the participant before getting the information.

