### Patients and enrollment

Women with PCOS and IR will be recruited from the Department of Traditional Chinese Medicine in the First Affiliated Hospital of Guangzhou Medical University, Xuzhou Maternity & Child Health Hospital, Dalian Municipal Women and Children’s Medical Center, Guangdong Women and Children’s Hospital, *and* Hexian Memorial Affiliated Hospital of Southern Medical University if they meet the inclusion criteria and do not have any exclusion criteria. Eligible subjects will be approached and sign the consent form after detailed explanation of the study design and comprehensive counseling (see the flow diagram in Fig. 1).

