### Statistical analysis strategy

The Kolmogorov-Smirnov test will be used to test the normal distribution of continuous variables. Continuous variables will be presented by mean ± standard deviation if they are normally distributed or by median with interquartile range if they are not normally distributed. Both per protocol (PP) analysis and intention-to-treat analysis (ITT) will be used to determine the robustness of the evidence. Analysis of variance (ANOVA) with Bonferroni corrections will be used for comparing the differences between groups of continuous data in accordance with a normal distribution or Kruskal-Wallis test for non-normal distribution data when appropriate; χ^2^ tests will be used for comparison of dichotomous data. For the primary outcome, analysis of covariance (ANCOVA) (accompanying LSMEAN and 95% CI) will be used. ANOVA will be used to calculate the changes from baseline to after treatment and follow-up, respectively, and it will also be used to compare the differences between treatment arms with respect to the primary outcome, HOMA-IR. Effect of continuous data will be reported by both *P*-value and mean difference with 95% confidence interval and categorical data by *P*-value and relative risk (RR) and risk difference (RD) with 95% confidence interval; the number needed to treat (NNT) will be calculated if there is statistical significance between groups. All statistical analyses of the data will be performed by using SPSS software version 21.0 (SPSS Inc., Chicago, IL, USA).

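### Five hospitals recruit but randomisation is stratified on three sites, so the allocation rule does not fit the site list; hospital should also be named in the primary model

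*Protocol article*

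**What the plan says.** Patients and enrollment lists the recruiting hospitals in one sentence. It opens with "Women with PCOS and IR will be recruited from the Department of Traditional Chinese Medicine in the First Affiliated Hospital of Guangzhou Medical University", continues with "Xuzhou Maternity & Child Health Hospital, Dalian Municipal Women and Children’s Medical Center, Guangdong Women and Children’s Hospital", and ends with "Hexian Memorial Affiliated Hospital of Southern Medical University if they meet the inclusion criteria". That is one hospital, then three, then one: five in all.

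Randomization and patient allocation states that subjects are "randomly allocated into one of the three treatment arms by a 1:1:1 treatment ratio" through a central system, and then: "Patients will be stratified based on three sites and randomly assigned". The three sites are not named, and the section does not mention hospitals outside those three.

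Statistical analysis strategy says: "For the primary outcome, analysis of covariance (ANCOVA) (accompanying LSMEAN and 95% CI) will be used". It lists no covariate or factor. A later sentence there turns to ANOVA and says that "it will also be used to compare the differences between treatment arms with respect to the primary outcome, HOMA-IR". It gives no model terms either.

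**The concern.** A site-stratified allocation needs a rule for every site that enrols. With five hospitals and three strata, at least two hospitals have no stated rule. Either they share a stratum with another hospital, or their patients are randomised outside the stratification, or one of the two counts is out of date. A reader cannot tell which, and a later analysis plan cannot settle it, because stratification is built into the allocation as patients are randomised.

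Site is a plausible source of variation in this trial. Stimulation intensity and needle depth are adjusted patient by patient (Needles and stimulation), and the acupuncturists know whether they are giving true or sham treatment (Randomization and patient allocation). If a hospital is not a stratum of its own, its arm counts can drift apart by chance. If site is a stratification factor but is not in the model, the standard error does not reflect the balance that the design bought.

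**Working it through.** **1. Count of sites.** Hospitals named under Patients and enrollment: 1 + 3 + 1 = 5. Sites used as strata under Randomization and patient allocation: 3. Difference: 2. No other section of the article links the two numbers.

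**2. What the mismatch could mean.** The text allows three readings:
- Three strata cover all five hospitals, with some pooled. Every patient is stratified, but more coarsely than by hospital.
- Three hospitals are strata and two are not. Patients from the two are randomised without within-hospital balance.
- The central system stratifies by all five, and the word three is left over. Only the text is wrong.

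If recruitment were equal (assumption), three strata would hold 342/3 = 114 patients each and five would hold 342/5 = 68.4, so five strata are workable with three arms.

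**3. Base case for the power figures.** Sample size calculations gives a pilot mean of 4.3, a later SD of 2.1 and an anticipated 20% difference. Reading that difference as 0.20 × 4.3 = 0.86 (assumption), with SD 2.1, two-sided α of 0.05 and 80% power, the normal formula gives 94 per group and the t-based one gives 95. This reproduces the plan's 95 per group before attrition. Its normal-approximation power is 80.6%:
- standardised effect = 0.86 / (2.1 × √(2/95)) = 2.822
- power = Φ(2.822 − 1.960) = 0.806

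**4. Effect of omitting site after stratified allocation.** Let ρ be the share of outcome variance explained by site. The article gives no value, so ρ is an assumption throughout. Arms are taken to be balanced within site.
- Reported SE / true SE = 1/√(1 − ρ)
- True α = 2 × [1 − Φ(1.960/√(1 − ρ))]
- Power without site = Φ(2.822/√(1 − ρ) − 1.960/√(1 − ρ))
- Power with site = Φ(2.822/√(1 − ρ) − 1.960)

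| ρ (assumed) | SE too large by | True α | Power without site | Power with site |
|---|---|---|---|---|
| 0.05 | 1/√0.95 − 1 = 2.6% | 0.044 | 81.2% | 82.5% |
| 0.10 | 1/√0.90 − 1 = 5.4% | 0.039 | 81.8% | 84.5% |

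At ρ = 0.01 the true α is 0.049 and power is 80.7% without site against 81.0% with it. At ρ = 0.15 the true α is about 0.034 and power is 82.5% against 86.5%.

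**5. Room to act.** Trial status reports 114 randomised by the end of December 2016. Of 342 planned, 342 − 114 = 228 were still to be allocated, which is two thirds.

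**6. Cost of the model term.** Five hospitals as a fixed factor use 5 − 1 = 4 degrees of freedom.

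**The case against.** A reader might infer that site has been left out of the primary model. The article does not support that. It names ANCOVA, which has at least one covariate by definition, and lists none, not even baseline HOMA-IR. The list is abbreviated, and a condensed article may leave it to an analysis plan that is not shown. Site is therefore unspecified. The absence of the list is not a fault in itself; naming hospital is a recommendation that follows from the stratified design.

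A reader might also infer that two hospitals are certainly unstratified, or that they are small centres prone to imbalance. The article says neither. Pooling would leave every patient stratified, and no recruitment by centre is reported.

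The two possible harms also do not fall fully on the same patients. An oversized standard error arises where allocation was balanced within site; chance imbalance arises where it was not. In an unstratified hospital the ordinary standard error already allows for that chance imbalance, so the unadjusted comparison stays valid.

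Finally, the quantities are small. On the assumed 5-10% share, power without a site term still exceeds the planned 80%. If the ANCOVA adjusts for baseline HOMA-IR, some between-hospital variance may already be removed, which would make the gain smaller. It would also be premature to change the central system before establishing what it does.

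All of this stands. None of it reconciles five hospitals with three strata: the article states both numbers, so the mismatch is more than omitted detail.

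**Conclusion.** The point holds as an internal contradiction: five recruiting hospitals against three stratification sites, with no statement of which three or how the remaining patients are allocated. That part rests on a count and needs no assumption.

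The modelling part is a modest improvement. Under an assumed 5-10% site share of the outcome variance and balance within site, omitting site would make the standard error 2.6-5.4% too large. True α would be about 0.044-0.039 in place of 0.05, and the power forgone would be about 1.3 points (82.5 − 81.2) to 2.7 points (84.5 − 81.8). The error is on the conservative side, so a reader who inferred a raised false-positive risk would be mistaken. The required sample size does not change.

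**What to change.** 1. Reconcile the two sections. State what the central system actually does: which sites are strata, and how patients from every recruiting hospital are allocated. If all five hospitals are already strata, this is a correction of text only.
2. If the system does not already stratify by all five, set hospital (five levels) as the stratification factor for patients still to be randomised, and record the date of the change. Allocations already made stand. Because randomisation is central, this is a system setting.
3. Name hospital as a fixed factor in the primary ANCOVA for all patients, including those randomised before any change. This costs one model term and at most four degrees of freedom. The separate ANOVA comparison of arms on HOMA-IR should be described consistently with that model.

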### Statistical analysis strategy

The Kolmogorov-Smirnov test will be used to test the normal distribution of continuous variables. Continuous variables will be presented by mean ± standard deviation if they are normally distributed or by median with interquartile range if they are not normally distributed. Both per protocol (PP) analysis and intention-to-treat analysis (ITT) will be used to determine the robustness of the evidence. Analysis of variance (ANOVA) with Bonferroni corrections will be used for comparing the differences between groups of continuous data in accordance with a normal distribution or Kruskal-Wallis test for non-normal distribution data when appropriate; χ^2^ tests will be used for comparison of dichotomous data. For the primary outcome, analysis of covariance (ANCOVA) (accompanying LSMEAN and 95% CI) will be used. ANOVA will be used to calculate the changes from baseline to after treatment and follow-up, respectively, and it will also be used to compare the differences between treatment arms with respect to the primary outcome, HOMA-IR. Effect of continuous data will be reported by both *P*-value and mean difference with 95% confidence interval and categorical data by *P*-value and relative risk (RR) and risk difference (RD) with 95% confidence interval; the number needed to treat (NNT) will be calculated if there is statistical significance between groups. All statistical analyses of the data will be performed by using SPSS software version 21.0 (SPSS Inc., Chicago, IL, USA).

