**Methods:**

This study is a multi-center, controlled, double-blind, and randomized clinical trial aiming to evaluate the effect of acupuncture on the insulin sensitivity in PCOS combined with IR. In total 342 patients diagnosed with PCOS and IR will be enrolled. Participants will be randomized to one of the three groups: (1) true acupuncture + metformin placebo; (2) sham acupuncture + metformin, and (3) sham acupuncture + metformin placebo. Participants and assessors will be blinded. The acupuncture intervention will be given 3 days per week for a total of 48 treatment sessions during 4 months. Metformin (0.5 g per pill) or placebo will be given, three times per day, and for 4 months.

Primary outcome measures are changes in homeostasis model assessment of insulin resistance (HOMA-IR) and improvement rate of HOMA-IR by oral glucose tolerance test (OGTT) and insulin releasing test (Ins). Secondary outcome measures are homeostasis model assessment-β (HOMA-β), area under the curve for glucose and insulin, frequency of regular menstrual cycles and ovulation, body composition, metabolic profile, hormonal profile, questionnaires, side effect profile, and expectation and credibility of treatment.

Outcome measures are collected at baseline, at the end of treatments, and 3 months after the last acupuncture treatment. On completion of the screening visit, randomization will be conducted using a central randomization system.

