### Intervention arms

#### Information to all study subjects

All participants will be advised about the importance of regular physical exercise and a balanced diet by a trained dietician before they receive the treatments. Importantly, they are instructed not to change their exercise or diet habits during the entire study period.

True acupuncture or sham acupuncture and metformin will be started 2 days after the baseline visit including OGTT and Ins. All subjects will be asked to use a barrier method for contraception. True and sham acupuncture treatment will be given three times per week. Each treatment session lasts for 30 min and can be separated by an interval of 1-3 days, with a maximum of 48 treatment sessions during 4 months. After the third treatment, all patients fill in the expectation and credibility questionnaire [31]. Metformin (0.5 g per pill) or placebo will be given, three times per day for 4 months.

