### Sample size calculations

In our pilot study [25] evaluating the effect of acupuncture on insulin sensitivity in PCOS women with IR, HOMA-IR reduced significantly after 3 months of acupuncture treatment when an interim analysis was performed and changed from (4.3 ± 2.5) vs. (3.7 ± 2.1). HOMA-IR ≥2.14 was considered to be abnormal. We anticipate that the HOMA-IR after 4 months of true acupuncture treatment will decrease 25%, and sham acupuncture will be decreased 5% as it is well known that sham is not an inert procedure. Therefore, the difference is 20%, with two-sided α assigned to be 5% and β 20% at the upper limit, respectively, at which the power is 80% and the rate of attrition estimated to be 20%. Thus, the sample size has been inflated from 95 to 114 per group, totaling 342 cases for the three arms. The sample size was calculated using the software statistics toolkit supported by the Department of Obstetrics and Gynecology of the Chinese University of Hong Kong (http://www.obg.cuhk.edu.hk/ResearchSupport/StatTools/index.php).

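### Continuous secondary outcomes that have a baseline value are compared without baseline adjustment, which is valid but less precise than the ANCOVA named for the primary outcome

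*Protocol article*

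**What the plan says.** The section Statistical analysis strategy sets the method for continuous outcomes in general: "Analysis of variance (ANOVA) with Bonferroni corrections will be used for comparing the differences between groups of continuous data" when they are normally distributed, otherwise "Kruskal-Wallis test for non-normal distribution data when appropriate". It then makes one specific assignment: "For the primary outcome, analysis of covariance (ANCOVA) (accompanying LSMEAN and 95% CI) will be used". No secondary outcome is given a model with a covariate.

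The next sentence brings baseline in by another route: "ANOVA will be used to calculate the changes from baseline to after treatment and follow-up, respectively". It goes on: "it will also be used to compare the differences between treatment arms with respect to the primary outcome, HOMA-IR". It does not say whether the analysis of changes extends to the secondary outcomes or concerns HOMA-IR alone.

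The baseline data exist. The abstract states: "Outcome measures are collected at baseline, at the end of treatments, and 3 months after the last acupuncture treatment". Table 3, with the sections on the baseline visit and on the two later visits, shows these measured before treatment, after 4 months of treatment and 3 months later:

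- the glucose and insulin tests
- body measurements, FG score and acne
- sex hormones and SHBG
- lipids
- questionnaires

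Not every secondary outcome is in that position. On expectation and credibility, Information to all study subjects says: "After the third treatment, all patients fill in the expectation and credibility questionnaire". The side-effect profile has no pre-treatment value, and Table 3 lists HbA1c at screening only.

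**The concern.** Neither one-way ANOVA nor Kruskal-Wallis takes a covariate. If follow-up values are compared, the part of the between-patient spread that the baseline value could explain stays in the error term, and a chance imbalance at baseline stays in the estimate. If changes are compared, the baseline is subtracted with a fixed weight of one. That over-corrects when baseline and follow-up are only modestly correlated.

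ANCOVA estimates the weight from the data. The plan already uses ANCOVA for HOMA-IR, so the secondary outcomes get a less efficient method although the information needed for the better one is collected. What is at stake is the width of the secondary confidence intervals and the chance of detecting real differences between arms.

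**Working it through.** **Inputs.** The plan's only quantitative target is for HOMA-IR (Sample size calculations): a 20% difference, two-sided alpha 5%, power 80%, and pilot values that "changed from (4.3 ± 2.5) vs. (3.7 ± 2.1"). It states no power and no baseline-to-follow-up correlation (rho) for any secondary outcome. Rho is therefore an assumption, shown as a range.

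**The plan's own figure.** Difference = 0.20 × 4.3 = 0.86; SD = 2.1.

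n per group = 2 × (1.96 + 0.8416)² × (2.1/0.86)² = 2 × 7.849 × 5.963 = 93.6, so 94. The t-based version gives 94.6, so 95, which is the stated number before attrition. It corresponds to an unadjusted comparison of two means and to a standardised effect of 0.86/2.1 = 0.41.

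**Precision of the three analyses.** Variance of a treatment contrast, in units of the variance with follow-up values alone, assuming equal variances at both times:

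- ANOVA on follow-up values: 1
- ANOVA on changes: 2(1 − rho)
- ANCOVA on the follow-up value with baseline as covariate: 1 − rho²

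Follow-up minus ANCOVA is rho². Change minus ANCOVA is 2(1 − rho) − (1 − rho²) = (1 − rho)². Both are positive for any rho strictly between 0 and 1.

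The interval-width ratio is the square root of the variance ratio:

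| rho | Change | ANCOVA | Follow-up/ANCOVA | CI wider | Change/ANCOVA | CI wider |
|---|---|---|---|---|---|---|
| 0.3 | 1.40 | 0.91 | 1.10 | 5% | 1.54 | 24% |
| 0.5 | 1.00 | 0.75 | 1.33 | 15% | 1.33 | 15% |
| 0.7 | 0.60 | 0.51 | 1.96 | 40% | 1.18 | 8% |
| 0.8 | 0.40 | 0.36 | 2.78 | 67% | 1.11 | 5% |

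At rho 0.5, either form of ANOVA needs 1/0.75 = 1.33 times as many patients to match ANCOVA.

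**In terms of power.** Take a secondary outcome with the same standardised effect of 0.41, 95 patients per arm, and two-sided 5% without Bonferroni. Follow-up ANOVA has 81% power. At rho 0.3, 0.5 and 0.7, change-score ANOVA has 67%, 81% and 95%, and ANCOVA has 84%, 90% and 98%. This only illustrates scale, since the plan makes no power claim for secondary outcomes.

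**Equal variances.** Let k be baseline SD over follow-up SD. The change variance is then 1 + k² − 2k·rho, which exceeds 1 − rho² by (k − rho)². This is never negative, so the direction does not depend on the assumption. With the pilot HOMA-IR SDs as an example, k = 2.5/2.1 = 1.19. At rho 0.5 the change variance is (6.25 + 4.41 − 5.25)/4.41 = 1.23 against 0.75 for ANCOVA.

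These formulas describe ANOVA. The loss with Kruskal-Wallis was not calculated.

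**The case against.** A reader might infer that the secondary analyses ignore baseline altogether. The text does not support that, because it also describes ANOVA of changes from baseline. Its scope is unclear, but nothing says that secondary outcomes are compared on raw follow-up values. If changes are analysed, the loss is smaller at high correlation: at rho 0.95 the variances are 2(0.05) = 0.10 and 1 − 0.9025 = 0.0975, a saving of 2.5%. A saving of about 90% at that rho holds only against follow-up values. This objection reduces the size of the loss but does not remove it.

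A reader might also infer that every secondary outcome is affected. That is too broad, since some have no baseline value.

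Nor are the planned comparisons biased or invalid. Under randomisation both forms of ANOVA are sound, and chance imbalance is already reflected in the standard error. The point concerns efficiency only.

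It can be said that covariates for secondary outcomes are left to a fuller analysis plan, which may exist. That would answer a complaint about missing detail. Here, however, the article states a general method and sets the primary outcome apart from it.

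Finally, Kruskal-Wallis is robust to skewness and outliers, and a log scale cannot be applied directly to acne counts or FG scores, which can be zero. Both points stand and limit the remedy. Against this, Kruskal-Wallis does not itself supply the mean difference and confidence interval that the same section promises for continuous data.

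**Conclusion.** The point holds as a matter of precision. Continuous secondary outcomes with a baseline measurement are assigned methods without baseline adjustment, or at best change scores. Relative to ANCOVA, intervals are about 5% to 67% wider as rho goes from 0.3 to 0.8 if follow-up values are compared, and about 24% falling to 5% wider over the same range if changes are compared.

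These figures rest on equal variances and an assumed rho, so the loss for any particular outcome is unknown. It is small where rho is low and follow-up values are used, or where rho is high and changes are used. The direction holds for any rho strictly between 0 and 1 under equal variances. The change is worth making, but its absence does not invalidate the secondary results.

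**What to change.** In Statistical analysis strategy, state that arms are compared on each continuous secondary outcome with a baseline value by ANCOVA. The month-4 value is the response, with a corresponding analysis at month 7. Treatment arm and the outcome's own baseline are the terms, and the Bonferroni correction is kept.

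- **Positive, skewed outcomes:** analyse on the log scale and report a ratio with its interval.
- **Skewed outcomes that can be zero (acne counts, FG score):** use a rank-based ANCOVA, or ANCOVA on the original scale with Kruskal-Wallis kept as a sensitivity analysis.
- **Outcomes without a baseline (expectation and credibility, side effects):** leave as planned.

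The change needs no extra visit, sample or patient, and ANCOVA is already planned for the primary outcome. By the end of December 2016, 114 of the 342 participants had been randomised (Trial status), so the wording could be settled well before the data were complete. The one small downside is that log-scale results are ratios, so the sentence promising mean differences for continuous data needs a matching exception.

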As an integrated part of Traditional Chinese Medicine and a relatively safe treatment [19], acupuncture treatment for PCOS has gained increasing attention in recent years. The effect of acupuncture is most likely mediated via activation of sensory nerve fibers, which in turn modulate the sympathetic activity to the ovaries and in the central nervous system [20, 21]. A review found that acupuncture can correct various metabolic disorders contributing to the development of IR, such as hyperglycemia, overweight, hyperphagia, hyperlipidemia, inflammation, altered activity of the sympathetic nervous system, and insulin signal defect [22]. Thus, acupuncture may have the potential to improve insulin sensitivity [22]. Other findings suggest that electrical acupuncture stimulation affects more functional signaling pathways related to insulin sensitivity, while manual stimulation of acupuncture needles has a greater effect on glucose tolerance [23]. Furthermore, in female insulin-resistant rats both electrical and manual acupuncture stimulation enhances insulin sensitivity via activation of sensory afferents [24]. Our prospective pilot study (ClinicalTrials.gov NCT02026323) [25] of acupuncture affecting the insulin sensitivity in 81 cases of women with PCOS with IR showed that acupuncture has a significant effect on improving the insulin sensitivity in these patients. But there is still no randomized controlled trial to determine the effect of acupuncture on insulin sensitivity in women with PCOS combined with IR.

Thus, we present the protocol of a randomized controlled trial to investigate the effects of acupuncture on the insulin sensitivity of women with PCOS combined with IR. We hypothesize that true acupuncture is superior to metformin and sham acupuncture in improving insulin sensitivity.

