### Objectives

The primary objective of this randomized controlled trial is to evaluate the hypothesis that true acupuncture + metformin placebo (group 1) improves insulin sensitivity, as measured by changes in the homeostasis model assessment of insulin resistance (HOMA-IR), more effectively than sham acupuncture + metformin (group 2) and sham acupuncture + metformin placebo (group 3) in women with PCOS and IR. Secondary objectives include changes in HOMA-β (islet β-cell function), C-peptide index, the insulin response to glucose calculated from the oral glucose tolerance test (OGTT) and insulin releasing test (Ins), frequency of the regular menstrual cycle and ovulation, circulating sex steroids, lipid profile, health-related quality of life and symptoms of anxiety and depression, side effects, and credibility.

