### Outcome measures

#### Primary outcome

Change in HOMA-IR.

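### Two between-arm analyses with different multiplicity handling, ANCOVA and Bonferroni-corrected ANOVA, are both assigned to the primary outcome, and neither is named as deciding

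*Protocol article*

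**What the plan says.** The Primary outcome section of the protocol article names "Change in HOMA-IR". (The abstract also lists the HOMA-IR improvement rate as primary; that is a separate matter.)

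The hypothesis has two contrasts. The Background says "We hypothesize that true acupuncture is superior to metformin and sham acupuncture in improving insulin sensitivity". The Objectives say that true acupuncture plus metformin placebo improves insulin sensitivity "more effectively than sham acupuncture + metformin (group 2) and sham acupuncture + metformin placebo (group 3").

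The Statistical analysis strategy, a single paragraph, then gives three statements that bear on this outcome:

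- For continuous data in general: "Analysis of variance (ANOVA) with Bonferroni corrections will be used for comparing the differences between groups of continuous data".
- For the primary outcome: "For the primary outcome, analysis of covariance (ANCOVA) (accompanying LSMEAN and 95% CI) will be used". No correction is mentioned.
- For ANOVA again, after changes from baseline: "it will also be used to compare the differences between treatment arms with respect to the primary outcome, HOMA-IR".

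The Sample size calculations section derives the trial size from a 25% fall under true acupuncture and a 5% fall under sham, "with two-sided α assigned to be 5% and β 20% at the upper limit". It gives no metformin effect.

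**The concern.** ANCOVA and ANOVA are both assigned to the between-arm comparison of the primary outcome. One comes with no stated correction. The other comes, on the natural reading of the paragraph, with Bonferroni. The text does not rank them, does not say how many comparisons Bonferroni covers, and does not say whether it extends to the ANCOVA contrasts.

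The other signals do not settle the matter. The 'and' in the hypothesis points to a rule that both contrasts must win, under which Bonferroni has no function. Bonferroni points to a rule that any one contrast may win. The sample size points to one contrast at an uncorrected level.

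At stake is the headline verdict. A true-versus-sham result with a p-value just below 0.05 is positive by one stated route and negative by the other, and the choice could be made after the data are seen.

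**Working it through.** **Inputs from the Sample size calculations section.** Pilot HOMA-IR "changed from (4.3 ± 2.5) vs. (3.7 ± 2.1"); falls of 25% and 5%; two-sided α 5%; power 80%; 20% attrition; 95 inflated to 114 per group. The section does not say which SD was used.

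**Step 1: reproduce the plan's figure.** The difference is 0.20 × 4.3 = 0.86. With SD 2.1,

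n = 2 × (1.960 + 0.842)² × 2.1² / 0.86² = 93.6, so 94 per group; the t-based version gives 94.6, so 95.

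The stated 95 is reproduced as one contrast, true versus sham, at unadjusted two-sided 5%. With the same inputs, 80% power would need 115 evaluable per group under Bonferroni over two comparisons and 127 over three. The sample size therefore carries no correction.

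**Step 2: how often the two routes disagree.** Evaluable per arm: 114 × 0.80 = 91. SE of a difference = 2.1 × √(2/91) = 0.311. Expected z = 0.86 / 0.311 = 2.76.

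| Level | Critical z | Smallest significant difference | Power, true vs sham |
|---|---|---|---|
| 5%, unadjusted | 1.960 | 0.61 | 78.9% |
| 2.5%, divisor two (assumed) | 2.241 | 0.70 | 69.9% |
| 1.67%, divisor three (assumed) | 2.394 | 0.75 | 64.4% |

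Significant unadjusted but not corrected:

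- divisor three: 78.9% − 64.4% = 14.5% of trials;
- divisor two: 78.9% − 69.9% = 9.0% of trials.

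Sensitivity: 95 per arm gives about 14.0% and 8.6%. SD 2.5 with 91 per arm gives about 17% and 11%.

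The same z-statistic is used for both routes, so this isolates the gap between thresholds. It does not model differences between ANCOVA and ANOVA, nor the precision gained from baseline adjustment.

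**Step 3: what each decision rule needs.** The two contrasts share the true-acupuncture arm, so with equal arms their correlation is 0.5.

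- *Both must win.* Each contrast tested at 5% keeps the error of the joint claim at or below 5%. No correction is needed.
- *Either may win.* Two uncorrected contrasts give a two-sided family-wise error of about 9.1%, or about 4.5% counting only false wins for acupuncture. All three pairs uncorrected give about 12.2%.

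**Step 4: cost of Bonferroni if both must win.** Joint power at 95 per group, with the SD set at 2.116 so that the sham contrast has exactly 80% power. The metformin fall is an assumption, shown as a range.

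| Assumed metformin fall | Each at 5% | Divisor two | Divisor three |
|---|---|---|---|
| 5% | 69% | 57% | 51% |
| 10% | 50% | 38% | 32% |
| 15% | 27% | 18% | 14.5% |
| 20% | 10% | 6% | 4% |

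**The case against.** The strongest reply is that 'and' already fixes the rule. The Background and Objectives both use it, the Discussion repeats it, and nothing in the article says either contrast would suffice. On that reading uncorrected ANCOVA is valid. This stands, and it rules out a stronger claim that a reader might infer: that the plan as written inflates type I error to 9% or 12%. Those figures need an either-may-win rule that the text never states. It also rules out saying that both routes are wrong.

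Second, the ANCOVA sentence is silent on correction; it does not say that the contrasts are unadjusted. Bonferroni, stated earlier in the same paragraph for continuous data, might be meant to cover it. That is possible, but it is exactly what cannot be settled from the text.

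Third, the divisor of three is not in the document. That stands: the 14.5% depends on it, which is why the smaller figure for two is shown as well.

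Fourth, a condensed article may leave a testing order to the analysis plan. Silence alone would be no finding. Here, however, the article does state a correction and two analyses for one outcome, and these do not fit together.

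A reader might also be tempted to dramatise the gap between rules by assuming that metformin works as well as acupuncture. Superiority to metformin is then false, and a both-must-win rule that rarely succeeds is behaving correctly. That is not evidence of lost power.

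**Conclusion.** The point holds as a conflict between stated rules. Two between-arm analyses, one with Bonferroni and one with no stated correction, are assigned to the primary outcome with neither ranked. The hypothesis, the correction and the sample size each imply a different decision rule.

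At the planned effect the two thresholds disagree on true versus sham in about 14.5% of trials if Bonferroni covers three pairs, and about 9% if it covers two. Both figures rest on 91 evaluable per arm and on SD 2.1, which is the pilot post-treatment SD and neither an SD of change nor a baseline-adjusted residual SD. If both contrasts must win, Bonferroni only costs power: about 11 to 18 percentage points of joint power if metformin's fall is 5% or 10%, both assumed values.

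The documents do not support a finding of actual error inflation. The trial remains interpretable, but the verdict should not be open to choice after the data are seen.

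**What to change.** Amend the Statistical analysis strategy before unblinding:

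1. Name the ANCOVA as the sole deciding analysis of the primary outcome, with the ANOVA as supportive.
2. Drop Bonferroni for the primary outcome.
3. Test true acupuncture against sham plus placebo at two-sided 5%. Only if that is significant, test true acupuncture against sham plus metformin at two-sided 5%. Report unadjusted 95% confidence intervals for both.
4. Claim superiority to metformin and sham only if both tests pass. If only the first passes, limit the claim to sham.
5. Report metformin versus sham outside the confirmatory family.

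This order keeps family-wise error at 5% and matches the contrast and level that reproduce the sample size. Simply declaring that both contrasts must win would also be valid and stays closer to the stated hypothesis; the sequence additionally permits a separate claim against sham.

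The cost is a few sentences and no new data. The Trial status section reports 114 of the planned 342 participants randomized by the end of December 2016. The downside is that if the sham contrast fails, the metformin contrast is descriptive only.
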